### Interventions

The training sessions are conducted in small groups ranging from 3 to 7 participants by the same investigators throughout the study. A detailed description of each intervention is provided below:

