### Sample size

The sample size calculation was performed using the GPower v. 3.1 software, adopting a significance level of *α* = 0.05 and a power of 80%. Data used in the determination of the effect size *f* for each primary outcome (cognitive capacity: *f* = 0.35; dynamic balance: *f* = 0.22; dual-task performance: *f* = 0.20) were extracted from [16, 29], resulting in a total sample size of 52 participants. To account for possible losses during the study procedures, ten additional participants (i.e., ~ 20%) are to be recruited for the study, totaling 62 participants randomized between the two groups.

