### Randomization, assignment of interventions, and blinding

Participants included in the study are first stratified based on their MMSE score and then randomized in a 1:1 ratio between the two groups using blocks of different sizes. Randomization is performed on the www.randomization.com website by an investigator ([name]) not involved with the assessments and training of the participants after the baseline measurements are completed. The same investigator is responsible for contacting each participant by telephone to inform which group he/she is allocated to and provide detailed information on the days and time that the online training sessions will occur. Blinding is applied to the primary and secondary outcome assessors at baseline, and a similar procedure will also be applied at the post-intervention assessment procedures. Due to the nature of the interventions, the team conducting the exercise sessions and the participants performing them cannot be blinded.

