### Statistical analysis

Analyses will be performed using the SPSS software v. 25.0, adopting an *α* = 0.05. Descriptive data will be presented as means, standard deviations, 95% confidence intervals, or absolute and relative frequencies. Data normality will be tested by the Shapiro–Wilk test, and the Levene test will test the homogeneity of variances. Primary and secondary outcome analyses will be conducted using mixed linear models with “treatment group x timepoint” interaction terms and using baseline values as covariates. An intention-to-treat analysis will include all randomized participants, in which missing data will be imputed using multiple imputations. In contrast, a per-protocol analysis will be performed with only those participants with an attendance rate  ≥ 80%. Effect sizes between-group will be computed based on Cohen’s *d* and the 95% confidence interval.

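### Training is delivered in groups of 3 to 7, but neither the stated model nor the sample size allows for training group, and the article does not say whether groups are stable or arm-specific

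*Protocol article*

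**What the plan says.** The opening of the Interventions section, placed above the descriptions of both arms, says: "The training sessions are conducted in small groups ranging from 3 to 7 participants by the same investigators throughout the study". Delivery lasts 12 weeks.

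Allocation is individual. Under Randomization, assignment of interventions, and blinding, participants are "randomized in a 1:1 ratio between the two groups using blocks of different sizes". The investigator who randomises then telephones each participant to give the allocation and "provide detailed information on the days and time that the online training sessions will occur". Only the combined arm (PCT) receives the weekly cognitive session.

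Under Statistical analysis, "Primary and secondary outcome analyses will be conducted using mixed linear models", with a treatment-group-by-timepoint interaction and baseline values as covariates. No term for training group is named, and the random-effects structure is not described.

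The Sample size section reports "adopting a significance level of *α* = 0.05 and a power of 80" per cent. The smallest of its three effect sizes is "dual-task performance: *f* = 0.20". It gives the outcome as "resulting in a total sample size of 52 participants", then adds ten for losses, "totaling 62 participants randomized between the two groups". No design effect is mentioned.

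**The concern.** People who train together for 12 weeks may end up more alike than people who do not. They share peers, a time slot and probably a calendar period. In the PCT arm, two weekly cognitive sessions (weeks 2 and 10 in Table 2) have each participant name animals. That is also the concurrent task in the primary dual-task test and the task in the verbal fluency outcome. If members hear one another's answers, practice on an outcome task is shared within the group.

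If outcomes cluster by training group and the analysis ignores it, the standard error of the arm comparison is wrong. With arm-specific groups, confidence intervals are too narrow, type I error exceeds 5%, and the planned power is overstated. The power calculation leaves almost no room to absorb this.

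**Working it through.** **Inputs from the article.** Two-sided α = 0.05 (sidedness is not stated, and an F test is taken as two-sided); power 80%; f = 0.20; two arms, two time points; 52 evaluable, 62 randomised (31 per arm); training-group size m from 3 to 7, midpoint 5.

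**Inputs assumed.** Correlation between repeated measures ρ = 0.5 (not given). ICC of the analysed outcome by training group from 0.01 to 0.10 (not given).

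**Step 1: reproduce 52.** For the within-between interaction in a repeated-measures ANOVA, λ = f² × N × 2 / (1 − ρ). At N = 52, λ = 0.04 × 52 × 2 / 0.5 = 8.32 on 1 and 50 degrees of freedom, which gives power 0.807. The smallest even N reaching 0.80 is 52. Other values of ρ do not give 52: ρ = 0, 0.3 and 0.7 give 102, 72 and 32. A one-way between-group ANOVA gives 200. The match uses no design effect, so the stated sample size behaves as a calculation for independent participants.

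**Step 2: stable, arm-specific groups.** Design effect DE = 1 + (m − 1) × ICC. The unadjusted standard error is too small by the fraction 1 − 1/√DE. Type I error is approximately 2 × [1 − Φ(1.96/√DE)]. Power uses λ/DE in Step 1. For m = 5:

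| ICC | DE | SE too small by | Type I error | Power at 52 | Evaluable N needed (52 × DE) |
|---|---|---|---|---|---|
| 0.01 | 1 + 4 × 0.01 = 1.04 | 2% | 5.5% | 0.79 | 55 |
| 0.05 | 1 + 4 × 0.05 = 1.20 | 9% | 7.4% | 0.73 | 63 |
| 0.10 | 1 + 4 × 0.10 = 1.40 | 15% | 9.8% | 0.67 | 73 |

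Reducing the sample to 52/1.4 ≈ 37 instead of dividing λ gives 0.66 in the last row.

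A simulation with 31 per arm in groups of 5, 5, 5, 5, 5 and 6, analysed by an unclustered t-test, gives type I error of 5.6%, 7.5% and 10.1% at the same ICCs. This agrees with the formula.

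**Step 3: dependence on group size.** Simulated type I error with groups mostly of 3, and with groups of 5 to 7:

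| ICC | Groups of 3 (one of 4) | Groups of 7, 7, 7, 5, 5 |
|---|---|---|
| 0.01 | 5.2% | 5.6% |
| 0.05 | 6.2% | 8.0% |
| 0.10 | 7.6% | 11.5% |

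**Step 4: groups that mix arms.** A shared group effect then largely cancels in the arm comparison, while the unadjusted variance still contains it. The test becomes slightly conservative: simulated type I error is about 4.9% at ICC 0.01, 4.5% at 0.05 and 4.1% at 0.10, with 12 groups split as evenly as possible between arms.

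**The case against.** **Stable membership is not stated.** A reader might infer fixed groups from the Interventions sentence, but the words about the whole study describe the investigators, not the members. Assigned days and times make stable groups plausible and no more. This objection stands.

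**Nesting within arm is not stated.** A reader might infer that standard errors are certainly too small. Nothing says whether physical sessions hold one arm or both, and Step 4 shows that the direction reverses if they mix. Scheduling after allocation makes arm-specific groups plausible. The cognitive sessions are arm-specific because only PCT attends them, provided they too are run in groups. The claim must therefore be conditional.

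**The sources of correlation are limited.** If the same investigators lead all sessions, a leader effect is a weak source of clustering. Blocked randomisation tends to balance calendar effects between arms. The cognitive tasks are mostly individual, and most of the 84 cognitive sessions are done alone at home. No figure in the article supports a particular ICC, and at 0.01 the effect is trivial. All of this stands and limits the size of the point.

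**The model may be completed elsewhere.** A reader might infer that the analysis definitely treats participants as independent. The article condenses a fuller plan, a mixed model can carry a training-group effect, and the random effects are not listed. That answers part of the point. It does not answer the sample size, which is stated here and is matched without a design effect. Nor does it settle how groups are formed, on which the right model depends.

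**The remedy has a price.** About six groups per arm leaves roughly 10 degrees of freedom for a group-level comparison: critical t of 2.23 against 2.00, an interval about 11% wider. This is a fair reason to accept a sensitivity analysis instead of a change to the primary model.

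**Conclusion.** The point holds in conditional form. Delivery is in groups, the stated model names no training-group term, and the sample size contains no design effect. If groups are stable and arm-specific and outcomes cluster, the error is negligible at an ICC of 0.01 and material at 0.05 to 0.10: type I error of about 7.4% to 10%, and power of 0.73 to 0.67 instead of 0.81. If groups mix arms, the unadjusted analysis is mildly conservative.

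These sizes rest on an assumed ICC, an assumed ρ of 0.5 and a group size of about 5. The type I figures come from a simple two-group comparison, not from the full baseline-adjusted model. Because planned power is only 0.807, even an ICC of 0.01 at group size 5 takes it just below 80%.

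**What to change.** 1. Record a training-group identifier for each participant, separately for physical and cognitive sessions if they differ. Attendance is already monitored, so session records may supply it.
2. State whether membership is stable and whether each type of group is arm-specific.
3. Fit training group as a random intercept, nested in arm if groups are arm-specific and crossed with arm if they are mixed, with Satterthwaite degrees of freedom. Do this in the primary model or as a prespecified sensitivity analysis. If baseline and week 13 both enter as outcome rows, let the term act on the change (training group by time), since an intercept common to both times cancels from the interaction.
4. Report the estimated ICC, and state that the 80% power assumes no clustering.

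The cost is one or two identifiers and one model term. With few groups per arm there are fewer degrees of freedom and a somewhat wider interval. The change makes the inference valid under clustering but does not restore lost power.

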#### Physical training only group

The PT group acts as an active control group that only perform the physical training intervention, which is presented in detail in Table 1. Specifically, participants assigned to this group receive two remotely supervised physical training sessions per week for a total of 12 weeks. Each session begins with a 5-min general warm-up and end with a 5-min stretching, whereas the main part has 20 min during the first training mesocycle (week 1) and progresses to up to 35 min at the end of the intervention (weeks 9–12). The exercises are performed in a circuit fashion at an intensity corresponding to 3 on Borg’s CR10 rating of perceived effort scale (i.e., moderate). Participants will be asked to arrange the space in which the exercise sessions are to be performed (e.g., their living room) with safety as a priority, ensuring the absence of any objects that may pose a risk of falling. Participants will also receive clear instructions to stay near a fixed structure or a chair, allowing them to stabilize themselves if they experience a sense of imbalance or the need to rest during the exercise sessions.

**Table 1 Tab1:** Physical training program periodization

Week	Exercise	Observations	Sets	Reps/duration	Rest between sets	Intensity
1	Single-leg balance	W/support	1	30″	-	3^a^
	Guided chair squat		1	10x		
	Wall push-ups		1	10x		
	Wall squat	Isometric	1	15″		
	Lateral shoulder raise		1	10x		
	Standing hip abduction	W/support	1	10x		
	Bent over row		1	10x		
	Plantar flexion		1	10x		
	Seated leg raise	Isometric	1	30″		
2–4	Single-leg balance	W/support	2	35″	2′	3
	Guided chair squat		2	12x		
	Wall push-ups		2	12x		
	Wall squat	Isometric	2	20″		
	Lateral shoulder raise		2	12x		
	Standing hip abduction	W/support	2	12x		
	Bent over row		2	12x		
	Plantar flexion		2	12x		
	Seated leg raise	Isometric	2	35″		
5–8	Single-leg balance	W/support	3	30″	2′	3
	Guided chair squat		3	10x		
	Sofa push-ups		3	10x		
	Wall squat	Isometric	3	15″		
	Lateral shoulder raise		3	10x		
	Standing hip abduction		3	10x		
	Bent over row		3	10x		
	Plantar flexion		3	10x		
	Seated leg raise	Isometric	3	30″		
9–12	Single-leg balance	W/support	3	35″	2′	3
	Free squat		3	12x		
	Sofa push-ups		3	12x		
	Wall squat	Isometric	3	20″		
	Lateral shoulder raise		3	12x		
	Standing hip abduction		3	12x		
	Bent over row		3	12x		
	Plantar flexion		3	12x		
	Seated leg raise	Isometric	3	35″		

^a^Borg’s CR10 scale

#### Physical and cognitive training group

The PCT group receives the same physical training intervention as the PT group. However, in addition to the two weekly physical training sessions, this group receives one additional remote cognitive training session per week for a total of 12 weeks, with at least 24 h separating it from the physical training sessions. Specifically, each cognitive training session begins with a 5-min conversation, followed by 45 min of cognitive exercises (described in detail in Table 2), and a 10-min final conversation including instructions for the participants. In addition to the cognitive exercises performed during this session, participants assigned to the PCT group receive a set of cognitive activities to be performed daily asynchronously (described in detail in Table 3), totaling 84 cognitive training sessions at the end of the intervention period.

**Table 2 Tab2:** Cognitive exercises that will be performed during the weekly cognitive training sessions

Week	Sets	Exercise	Duration
1	2	Write with the non-dominant hand two random sentences, chosen by the investigators	45′
2	3	Each participant must name the greatest number of animals as possible in one minute, which will be registered by the investigators	45′
3	2	Observe a random image and give it at least 5 different adjectives (up to 10)	45′
4	2	With a set of scrambled letters, try to form a word	45′
5	3	Read a word and think of five others that begin with the same letter	45′
6	3	Count from 0 to 100 backwards	45′
7	3	Count from 0 to 100 backwards saying only the even numbers	45′
8	1	Memorize what they need to buy in the market, without making a shopping list	45′
9	2	Read a sentence and make another sentence using the same words	45′
10	3	Each participant must name the greatest number of animals as possible in one minute, which will be registered by the investigators	45′
11	2	Observe a random image and give it at least 5 different adjectives (up to 10)	45′
12	3	Count from 0 to 100 backwards saying only the odd numbers	45′

**Table 3 Tab3:** Cognitive exercises that will be performed asynchronously throughout the intervention

Week	Daily frequency	Exercise	Duration
1–2	2	Get dressed with his/her eyes closed while seated	Indefinite
3–4	3	Brush his/her teeth using the non-dominant hand	Indefinite
5–6	2	See the time (i.e., clock) in a mirror	Not applicable
7–8	2	Eat using the non-dominant hand	Indefinite
9–10	2	Observe photos of his/her choice, upside down, while analyzing them	Not applicable
11–12	1	Turn off the lights in the house while singing	Indefinite

### Criteria for discontinuing allocated interventions

Participants may be discontinued from the study at any moment if they withdraw their consent to participate or report a lack of interest or unwillingness to continue the trial. In case the participant has already been allocated to any of the study arms, participation in the trial is interrupted if safety concerns such as a disease complication or a severe health event occurs that precludes attendance to the intervention sessions or in the case of medical request or advice.

### Trial retention strategies

Participants assigned to both groups are contacted the day before each training session via a standardized text message to remind them of the time the session is scheduled and to reinforce the importance of their participation in the intervention sessions. Additionally, phone calls or WhatsApp® messages are used to inquire participants about any adverse event that might have happened in the cases where a participant misses a training session without warning. Training sessions in which participants do not attend are not recovered, maintaining intention-to-treat analyses.

### Outcomes

Primary and secondary outcomes are assessed on three separate days, first at baseline (week 0) and then after the training intervention (week 13). Outcomes are assessed for all randomized participants, irrespective of attendance or completion status. Those who withdraw from the study at any time after randomization are also invited to perform the final study evaluations for inclusion in the intention-to-treat analysis.

The first testing day is held online. Participants answer an anamnesis, and the MMSE and IVCF questionnaires are applied. The second testing day also occurs online. During this session questionnaires related to the self-perceived quality of life, anxiety and depressive symptoms, occupational performance, working memory, and cognitive performance are applied individually by the investigators. Due to the personal nature of the data, assistance to complete the questionnaires is only provided by the investigators if completely necessary. On the third day, participants attend an in-person testing session at the Neuromuscular Assessment Laboratory of the Federal University of Pelotas. Dynamic balance, lower limb strength and endurance, handgrip strength, gait speed, and office blood pressure measures are performed. For all testing sessions, participants are instructed not to perform any intense physical activity 72 h before. Further, post-intervention measures are performed 72 h after the last training session. The temporal description of the study procedures is shown in Table 4.

**Table 4 Tab4:** Temporal description of the study protocol

		**Baseline**		**Intervention**	**Post-intervention**	
**Timepoint**	Week − 1	Week 0 (remotely)	Week 0 (in-person)	Weeks 1–12 (remotely)	Week 13 (remotely)	Week 13 (in-person)
***Enrolment***						
Eligibility screening	X					
Informed consent	X					
Allocation	X					
***Experimental conditions***						
Physical training (control)				X		
Physical and cognitive training				X		
***Assessments***						
*Primary outcome measures*						
MMSE		X				
Dual-task performance			X			X
*Secondary outcome measures*						
CFVI-20		X			X	
Timed Up-and-Go			X		X	X
Self-reported QoL		X			X	
Anxiety and depression		X			X	
Occupational performance		X			X	
Digit span		X			X	
Verbal fluency		X			X	
Handgrip strength			X			X
30-s Sit-to-Stand			X			X
Systemic blood pressure			X			X

*CFVI-20* Clinical-functional vulnerability index, *MMSE* mini-mental state examination, *QoL* Quality of life

The same investigators ([name] and [name]) are responsible for the application of the tests at both the baseline and post-intervention timepoints. Outcome assessors are trained, and a standard operating procedures manual is available to them during the testing procedures. Of note, outcome assessors and the investigators responsible for analyzing the primary and secondary outcomes listed in this protocol are blinded to the participant’s group.

### Primary outcomes measures

The primary outcomes of this study will focus on changes in cognitive function (as assessed by the MSSE score) and dual-task performance (measured during the TUG test) from baseline to post-intervention. This selection is motivated by the increased fall risk observed in older adults during concurrent tasks, such as walking while engaging in other cognitive or motor activities. Considering that daily life entails a wide range of dual- and multi-tasks, interventions that positively impact cognitive and functional outcomes are imperative for older individuals at a heightened risk of clinical-functional vulnerability [12].

#### Cognitive function

In addition to being an eligibility criterion for participants’ inclusion at baseline, the MMSE score is also used to assess cognitive function responses to the two training interventions investigated [29]. The questionnaire is divided into two sections: (1) the first requires verbal answers related to temporal and spatial orientation, memory, and attention, with a maximal score of 21 points; (2) the second section measures the ability to name objects, follow verbal and written commands, write a sentence spontaneously, and copy a complex polygon; a maximum score of 9 points is attributed to this section. The MMSE total score represents the sum of the scores from the two sections and ranges from 0 to 30 points [4]. Participants’ cognitive function is classified based on the education-adjusted cut-off scores as proposed by Brucki et al. 2003 [14].

#### Dual-task performance

To investigate older adults’ cognitive capacity and possible deficits, such as difficulty dividing attention or switching between tasks [1, 32], the TUG test is applied while simultaneously performing a verbal task to determine the influence of a cognitive task on physical function. Specifically, participants are asked to sit in a chair with a height of ≈ 46 cm, with their backs against the backrest and their hands on their legs. After the researcher’s signal, the participants should get up without using their arms, walk 3 m at their normal pace, turn around, walk back to the chair, and sit down until their backs are in touch with the backrest again [41]. During the procedure, participants must name the maximum number of animals possible, and the total number of animals recalled and the time to complete the test is recorded [16]. In addition, the dual-task cost is also calculated using the following formula: *Dual-task cost* = *[dual-task performance (s) – single-task performance (s) / single-task performance (s)* × *100]*, as previously described by [40].

### Secondary outcomes measurements

In addition to cognitive function and dynamic balance, a set of clinically relevant secondary outcomes for older adults were also established for this study and are described in detail below.

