**Methods:**

A randomized clinical trial will be conducted including 62 sedentary older individuals classified as at increased risk of clinical-functional vulnerability based on their Clinical-Functional Vulnerability Index score. Participants will be randomly allocated in a 1:1 ratio to one of two groups, an intervention group including physical training combined with cognitive training, or an active control group including physical training alone. Both groups will receive home-based supervised training remotely for 12 weeks and will be assessed for the primary and secondary outcomes of the study before and after the training period. Primary outcomes include cognitive function and dynamic balance with a dual task. Secondary outcomes encompass physical, cognitive, and occupational performance, functional capacity, quality of life, and anxiety and depression symptoms, as well as hemodynamic measures. Data analysis will be performed by intention-to-treat and per protocol using mixed linear models and Bonferroni’s post hoc (*α* = 0.05).

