#### Dynamic balance

The TUG test without a simultaneous cognitive task is applied for measuring dynamic balance. As previously explained, participants are asked to sit in a chair with a height of ≈ 46 cm, with their backs against the backrest and their hands on their legs. After receiving the orientation, the participants should get up without using their arms, walk 3 m at their normal pace, turn around, walk back to the chair, and sit down until their backs are in touch with the backrest again [41]. Those older adults who can perform the test in 10 to 20 s are considered independent. However, those who take longer than 20 s to complete the test are possibly in a state of postural instability and at higher risk for falls [38].

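### The protocol sizes three primary outcomes but defines two, does not say which dual-task quantity is primary, and sets 0.05 per outcome with no rule across the primaries

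*Protocol article*

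**What the plan says.** The article describes the primary outcomes in several places:

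- **Abstract, Methods:** "Primary outcomes include cognitive function and dynamic balance with a dual task". This is two outcomes, the second being the TUG done with a concurrent task.
- **Sample size:** effect sizes are given "for each primary outcome (cognitive capacity: *f* = 0.35; dynamic balance: *f* = 0.22; dual-task performance: *f* = 0.20". This is three outcomes, with dynamic balance listed apart from dual-task performance.
- **Primary outcomes measures:** cognitive function by MMSE, and "dual-task performance (measured during the TUG test) from baseline to post-intervention". Table 4 lists the same two as primary and puts Timed Up-and-Go under secondary.
- **Secondary outcomes measurements, lead-in:** "In addition to cognitive function and dynamic balance, a set of clinically relevant secondary outcomes for older adults were also established for this study". This sets the secondary outcomes apart from cognitive function and dynamic balance.
- **Dynamic balance, under the secondary heading:** "The TUG test without a simultaneous cognitive task is applied for measuring dynamic balance".

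Under Dual-task performance, "the total number of animals recalled and the time to complete the test is recorded", and a dual-task cost is then calculated from the dual-task and single-task times.

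On error rates, Sample size uses a significance level of 0.05 and 80% power. Statistical analysis sets 0.05 for everything and applies the same mixed model to primary and secondary outcomes. The Abstract attaches a Bonferroni post hoc to the mixed models. Statistical analysis does not mention it.

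**The concern.** A superiority trial should let a reader say in advance which results would confirm the hypothesis. Here single-task TUG is primary in the section that justifies the sample size and secondary in the sections that define the outcomes. Both cannot be right. A later analysis plan would first have to choose between them.

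The second primary is also named as a concept rather than a variable. Its three quantities can move in different directions: a participant may name more animals while walking more slowly.

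Finally, each outcome has the full 0.05, and nothing says whether one success is enough or all are needed. A report could then put forward single-task TUG, or whichever dual-task quantity was favourable, and cite a passage of this protocol in support.

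**Working it through.** **1. Reproduce the 52.** From Sample size: f = 0.35, 0.22 and 0.20; alpha 0.05; power 80%; two groups and two timepoints. The pre-post correlation is not stated; 0.5 is assumed. For a repeated-measures within-between interaction the noncentrality is λ = N f² m / (1 − ρ), with m = 2 timepoints, df1 = 1 and df2 = N − 2.

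For f = 0.20 and N = 52, λ = 52 × 0.04 × 2 / 0.5 = 8.32, and power is 80.7%.

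| Outcome in Sample size | f | N for 80% power at 0.05 |
|---|---|---|
| Cognitive capacity | 0.35 | 20 |
| Dynamic balance | 0.22 | 44 |
| Dual-task performance | 0.20 | 52 |

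So 52 matches the largest of three requirements, each at an unsplit 0.05. This supports reading Sample size as treating dynamic balance as a third primary. The match depends on ρ: for f = 0.20, N would be 72 at ρ = 0.3, 42 at 0.6 and 32 at 0.7.

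**2. Family-wise error if any one success counts.** For independent tests it is 1 − 0.95^k. For correlated tests it was simulated with equicorrelated normal statistics, two-sided at 1.96, with 1,000,000 draws. The correlations are assumptions.

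| Primaries | Independent | Correlation 0.5 | Correlation 0.9 |
|---|---|---|---|
| 2 (Primary outcomes measures) | 1 − 0.95² = 9.75% | 9.1% | 7.0% |
| 3 (Sample size) | 1 − 0.95³ = 14.3% | 12.5% | 8.4% |

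**3. Power under Holm with two primaries, N = 52, ρ = 0.5.** Each outcome first faces 0.025; once one passes, the other is tested at 0.05.

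- MMSE, f = 0.35: λ = 52 × 0.1225 × 2 / 0.5 = 25.48; power at 0.025 is 99.6%.
- Dual-task, f = 0.20: power is 80.7% at 0.05 and 71.6% at 0.025.
- Dual-task under Holm, taking the two tests as independent: 0.996 × 0.807 + 0.004 × 0.716 = 0.807.

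The power of dual-task time is essentially unchanged from the plan's own.

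**4. The alternative rule.** If both primaries had to succeed, no alpha adjustment would be needed. Power at 0.05 with N = 52 is 99.9% for f = 0.35, so joint power is about 0.999 × 0.807 = 81%. If all three had to succeed (87.5% for f = 0.22), it is about 0.999 × 0.875 × 0.807 = 71%, assuming independence. The article states no such rule.

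**The case against.** The strongest reply is that the list is less unstable than it looks. Only Sample size gives three primaries. The Abstract's phrase is the dual-task TUG and agrees with Primary outcomes measures and Table 4. The lead-in to the secondary outcomes may be shorthand for the same phrase. This largely stands, and the Abstract should not be counted as a conflict. It does not dispose of Sample size, which gives dynamic balance and dual-task performance different effect sizes and so cannot be naming one measure twice.

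On the dual-task variable, the cost formula expresses dual-task performance in seconds, and cost is introduced as an addition. Time is therefore the likely lead measure. That is a fair inference, but it remains one.

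A multiplicity rule may sit in an analysis plan that is not shown, and the article nowhere says that one success suffices. This is why the error rates above are conditional. The Abstract's Bonferroni does not settle the matter: as worded it belongs to comparisons within a model, not to the set of primary outcomes.

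Three stronger readings are tempting and are not supported:

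- **Four or five primary tests, with 18.5% or 22.6% family-wise error.** No passage makes every recorded quantity primary. Those figures also assume independence, which is impossible when cost is computed from the two TUG times.
- **Power falls to 72% once multiplicity is controlled.** That holds for dual-task only if MMSE is not significant at 0.025, which is improbable at the plan's own f = 0.35.
- **The loss allowance of about 20% is wrong.** Ten of 52 is 19%, so it is right on that denominator, and it has no bearing on the primary outcomes.

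**Conclusion.** The point holds as a contradiction in the primary list, an unnamed dual-task variable and an unsplit 0.05. Single-task TUG is primary in Sample size, and on its face in the lead-in to the secondary outcomes, but secondary where it is defined and in Table 4.

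If any single primary success is taken as a positive trial, the false-positive chance is about 9–10% for the two outcomes in Primary outcomes measures and 12.5–14% for the three in Sample size. These ranges run from correlation 0.5 to independence. At correlation 0.9 they fall to about 7–8%, still above 5%.

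The error rates rest on the any-one-counts reading, which the article neither states nor excludes. The power figures rest on the unstated correlation of 0.5, which is plausible because it reproduces 52. The contradiction itself rests on no assumption and needs correcting before the data are analysed.

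**What to change.** 1. Name two primary outcomes in every section: MMSE total score, and dual-task TUG completion time in seconds, both at week 13.
2. Remove dynamic balance from the primary outcomes in Sample size and in the lead-in to the secondary outcomes.
3. Make animals named, dual-task cost and single-task TUG explicitly secondary.
4. State in Statistical analysis that the two primaries are tested with Holm at a family-wise 0.05.
5. In Sample size, state the assumed correlation and that the total is driven by dual-task performance at f = 0.20.

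The planned number stays at 52 + 10, because dual-task time keeps about 80.7% power under Holm at a correlation of 0.5. The costs are a slightly stricter first-step threshold, power of about 72% for dual-task time if MMSE is not significant at 0.025, and an amendment to the ethics board and registry. Recruitment began in July 2022, so the amendment should be dated and made before any outcome comparison by group.
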